##### **11.2.1.2 Per-Protocol Analysis Set**

Not applicable.

##### **11.2.1.3 Safety Analysis Set**

The safety analysis set (SafAS) is defined as those subjects who received at least one dose of study vaccine. A safety analysis set is defined for each dose as the subset of subjects who received the dose.

Safety results will be presented according to the schedule received.

Subjects who received an inconsistent vaccination schedule (e.g. two primary injections of different dosages) will be assigned to the group determined by the first injection received. Their safety results after the second injection will be excluded from all safety analyses, and will be listed separately.

The SafAS for the booster vaccination is defined as those subjects who received at least one injection of the primo vaccination.

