#### **8.3.4 Handling of Missing Data and Outliers**

Missing safety data will not be replaced. All vaccinated subjects with safety data, and all safety data recorded in the CRFs will be included in the safety analyses. No search for outliers will be performed.

---

a Self-medication, such as over the counter medication.

b By convention, all solicited events will be considered as related to vaccination and referred to as reactions. For these reactions, the investigator's opinion will not be requested in the CRF.

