#### 11.1.1.2 Safety Analysis

The safety analysis will report the occurrence of solicited reactions and the incidence of unsolicited events over the safety observation period by vaccine formulation and by age group. The safety observation period is 21 days after each vaccination, and 7 days after each vaccination for the solicited reactions.

In order to avoid any under-estimation of the incidences, the number of subjects with documented safety will be used as denominator of the frequencies. For solicited reactions, safety summary parameters and EMEA safety criteria, 95% CIs of point estimates of proportion will be calculated using the exact binomial distribution (Clopper-Pearson method) for proportions (23).

***Safety combined for the 21 days after the first two vaccinations and after each separate vaccination (including booster):***

The analyses of safety will address the number and percentage of subjects, by vaccine formulation and by age group, experiencing injection site or systemic AEs until 21 days after each injection (solicited reactions from D0 to D7 and unsolicited AEs/reactions until D21).

The number and percentage of subjects experiencing the following will be described by vaccine formulation and by age group:

- Each solicited and unsolicited (MedDRA preferred term) reaction or event after each injection.
- Each solicited reaction (from 0 to 7 days) after each injection according to severity, time to onset, and number of days of occurrence.
- Each unsolicited adverse reaction (MedDRA preferred term) (until 21 days) after each injection according to severity, time to onset, and duration.

(Specific solicited reactions for each age group will be presented separately).

Additionally, for subjects aged  $\geq 2$  years, the number and percentage of subjects experiencing the following reactions (MedDRA Preferred Terms) in the 3 days following each injection will be reported by vaccine and age group after each injection (as defined in the Note for Guidance on Harmonization Requirements for Influenza Vaccines [CPMP/BWP/214/96]):

- Injection site induration  $>5$  cm observed for more than 3 days.
- Injection site ecchymosis (hemorrhage).

- Pyrexia: rectal equivalent temperature  $>38^{\circ}\text{C}$  for  $\geq 24$  hours (pyrexia).
- Malaise.
- Shivering (chills).

The number and percentage of subjects in each group experiencing SAEs will be collected throughout the study.

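### The safety set drops all results after a mismatched second primary injection from every safety analysis, against the protocol's own rule that all recorded safety data are analysed

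*Protocol*

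**What the plan says.** Protocol Section 11.2.1.3 puts everyone with at least one dose in the safety set and adds: "A safety analysis set is defined for each dose as the subset of subjects who received the dose". On grouping it says: "Safety results will be presented according to the schedule received". It then makes an exception: "Subjects who received an inconsistent vaccination schedule (e.g. two primary injections of different dosages) will be assigned to the group determined by the first injection". For these children it goes on: "Their safety results after the second injection will be excluded from all safety analyses, and will be listed separately". For the third injection the same section says: "The SafAS for the booster vaccination is defined as those subjects who received at least one injection of the primo vaccination".

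Section 8.3.4 gives the general rule: "All vaccinated subjects with safety data, and all safety data recorded in the CRFs will be included in the safety analyses". Section 11.1.1.2 gives the denominator rule, "In order to avoid any under-estimation of the incidences, the number of subjects with documented safety will be used as denominator of the frequencies", and the SAE summary, "The number and percentage of subjects in each group experiencing SAEs will be collected throughout the study". Sections 2.1 and 8.3.2 make SAEs over the whole study period an endpoint.

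**The concern.** A programmer who follows Section 8.3.4 and one who follows Section 11.2.1.3 will produce different safety tables from the same data, and nothing in the protocol says which section governs. If Section 11.2.1.3 is followed, a child's results leave the analysis because of what the child was given, although a safety set should describe exposure as it happened.

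The exclusion also has no stop point. Everything after the second injection covers the 21-day period, SAEs up to the booster, reactions to the booster and the 6-month follow-up. Safety is the first-listed objective (Section 2) and AE detection is the only basis for the sample size (Section 11.3), so the rule for who is counted should be unambiguous.

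The protocol itself foresees the situation. In Group 3 four volumes (0.25, 0.3, 0.5 and 0.6 mL) are drawn from two multidose presentations (Synopsis; Section 6.2.2, Table 6.1), so a half dose and a full dose come from the same presentation.

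**Working it through.** **1. The passages side by side.** Take a child whose second primary injection is of a different dosage from the first, with a reaction after the second injection and an SAE later.

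- Section 8.3.4: both events are analysed.
- Section 11.2.1.3, exclusion sentence: neither event is in any analysis; both are listed.
- Section 11.2.1.3, booster safety set: the child belongs to it, having had at least one primary injection. The exclusion sentence would still remove the child's booster results.
- Sections 2.1, 8.3.2 and 11.1.1.2: the SAE counts in the whole-study number and percentage. The exclusion sentence, read literally, removes it.
- Section 11.1.1.2, denominator: chosen so that incidence is not understated. In tables combining both primary injections, and in SAE tables, this child has documented safety from the first injection and can stay in the denominator while later events leave the numerator.

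**2. The plan's own figures.** Section 11.3 gives a probability above 90% (N=240) and of 70% (N=120) of seeing at least one AE of 1% incidence. With P = 1 − (1 − p)^N and p = 0.01:

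- N=240: 1 − 0.99^240 = 0.9104.
- N=120: 1 − 0.99^120 = 0.7006.

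Both reproduce.

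**3. Effect of exclusions on those figures.** The number of affected children, k, is not in the protocol. It is assumed here, with a range of 1 to 12, and all k are taken from the group in question.

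| k | N = 240 − k | N = 120 − k |
|---|---|---|
| 1 | 0.9095 | 0.6976 |
| 5 | 0.9058 | 0.6852 |
| 10 | 0.9009 | 0.6690 |
| 12 | 0.8989 | 0.6622 |

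A probability above 90% needs at least 230 children, so the overall statement fails only from k = 11. Even this overstates the loss, because these children still contribute after the first injection.

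**4. Effect within a cell.** Each combination of age group and dosage has 30 children (Synopsis, planned sample size). Suppose one child switches cells at the second injection and has one event after it, with no other such event. Intervals are Clopper-Pearson, the protocol's method.

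- Results after the second injection, grouped by dosage injected: the receiving cell has 30 + 1 = 31 children and shows 1/31 = 3.2% (95% CI 0.1% to 16.7%). Under the exclusion it shows 0/30 = 0% (95% CI 0% to 11.6%). The first-injection cell has 29 children after the second injection either way.
- Combined or SAE table, child kept in the first-injection group: 1/30 = 3.3% (95% CI 0.1% to 17.2%) with the event, and 0/30 = 0% (95% CI 0% to 11.6%) if the event is removed and the child remains in the denominator.

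**The case against.** The best defence is that a specific rule overrides a general one. Section 8.3.4 concerns missing data and outliers, while Section 11.2.1.3 deals with a rare case the general sentence did not have in mind. Reactions after a mixed schedule cannot be attributed cleanly to one formulation, which is a fair reason to show them apart, and in a descriptive trial without hypotheses no test is affected. The attribution point stands, but it supports a separate row, not removal from all analyses. The precedence is not written anywhere, and Section 8.3.4 allows no exception.

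A reader might infer that events are being hidden. They are not: the results are listed, each SAE goes to the sponsor within 24 hours (Section 9.1.1), and SAE data are reconciled before lock (Section 10.2). Nor does the text name SAEs as excluded. It speaks of safety results generally, so for SAE tables the conflict arises on a literal reading.

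A reader might also infer that the sample-size statement is undermined. Step 3 shows that it is not for any plausible number of cases, and an event in a listing has still been seen.

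Finally, the safety set defined for each dose may not support analysis by dosage. Section 6.1 uses doses for the injections of the series, so the phrase may mean first, second and booster injection. That objection stands and shapes the fix.

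**Conclusion.** The point holds as a contradiction in the text with a small expected numerical effect. Section 11.2.1.3 cannot be followed together with Section 8.3.4. Read literally, it also conflicts with whole-study SAE reporting and with its own booster safety set. What is lost is the place of these events in every count, percentage and interval, with possible understatement in combined and SAE tables.

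The size depends on how many children receive mismatched dosages, which the protocol does not state; few are likely. The detection probabilities are essentially unchanged (0.906 against 0.910 with five assumed exclusions). Within a cell of about 30, a single event moves the report between zero and about 3%. That figure assumes one affected child, one event and no other event in the cell.

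It would go too far to say that one exclusion turns 1/30 into 0/29 in the tables after the second injection. If results are grouped by the dosage injected, the child leaves the first cell in any case, and the comparison is 1/31 against 0/30 in the receiving cell.

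The text is wrong as written and should be corrected, but it does not threaten the trial's conclusions as a whole.

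**What to change.** Delete the exclusion sentence in Section 11.2.1.3 and make Sections 8.3.4 and 11.2.1.3 state one rule:

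- Children with mismatched primary dosages stay in the overall, combined-injection, SAE and booster safety summaries, with their events.
- Results after the second injection are summarised by the dosage actually injected, or in a separate mixed-schedule row that counts in the total. The protocol should choose one and say so, because the existing set for each dose may mean injection number.
- The children are flagged and listed in addition to being analysed. A sensitivity table without them is optional.

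The cost is one paragraph and minor programming, to be settled before the first partial database lock. The downside is small: a few records after the second injection follow a different first dosage, which the flag makes visible.

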### 5.3.6 Removal of Participants from Treatment or Assessment

Withdrawn subjects will not be replaced.

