#### 5.3.6.1 Conditions for Withdrawal

A subject may decide or a subject's parent/legal representative may decide for the subject to stop participating in the trial for any reason and at any time. In this case, the Investigator must determine that the reason for withdrawal is not related to an AE. The reason for a subject withdrawing during the trial will be specified in the source document and in the relevant section of the CRF.

Subjects/parents/legal representatives will be informed that they have the right to withdraw from the trial at any time.

The Investigator will discontinue the second or booster vaccination in the case of an event considered to be a definite contraindication (see following list). The vaccination will be delayed in the event of a temporary contraindication (see Section 5.3.5).

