### **11.2 Population to be Analyzed**

#### **11.2.1 Definition of Populations**

##### **11.2.1.1 Immunogenicity Analysis Set**

The immunogenicity analysis set (IAS) is defined for the immunogenicity descriptive analyses of the primo-vaccination, the Ab persistence, and the booster vaccination.

The IAS is defined as the subset of subjects who received the first vaccine injection.

The analysis of the primo-vaccination (see Section 11.1.2.2.1) addresses endpoints involving pre- and post-injection titers at D0, D21 and D42 for HI, SN methods. The analysis will include all available data.

Data from subjects excluded from this analysis set will be listed separately and the reasons for exclusion, as well as the circumstances of the missing data, will be examined.

Additionally, for the booster analysis, the IAS is defined as subjects having also received the booster injection.

The analysis will be performed according to the randomized vaccine formulation group.

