**Table 11.1: Populations for Analyses**

| Objectives                               | Description and Endpoints                                                                 |                                                    | Included and randomized subjects                          |
|------------------------------------------|-------------------------------------------------------------------------------------------|----------------------------------------------------|-----------------------------------------------------------|
| Safety objectives                        | Primo vaccination safety (solicited and unsolicited safety events)                        |                                                    | SafAS                                                     |
|                                          | Booster vaccination safety and safety follow-up (solicited and unsolicited safety events) |                                                    | SafAS                                                     |
| Immunogenicity objectives                | Primary series vaccination [D0-D42]                                                       | - HI (horse erythrocytes)                          | IAS                                                       |
|                                          | - Ab persistence                                                                          | - HI (turkey erythrocytes)
- Seroneutralisation | IAS                                                       |
|                                          | - Booster vaccination                                                                     |                                                    | IAS (available titers at pre- and post-booster timepoint) |
| Immunogenicity observationnal objectives | CMI response                                                                              |                                                    | CMI subset of IAS                                         |

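### The booster safety set does not require the booster, contradicting the per-dose definition in the same section and leaving unsolicited AE and SAE rates open to dilution

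*Protocol*

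**What the plan says.** Protocol Section 11.2.1.3 first defines the overall safety set as subjects with at least one dose of study vaccine. It then adds: "A safety analysis set is defined for each dose as the subset of subjects who received the dose". The section closes with: "The SafAS for the booster vaccination is defined as those subjects who received at least one injection of the primo vaccination".

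For immunogenicity, Section 11.2.1.1 takes a different line: "Additionally, for the booster analysis, the IAS is defined as subjects having also received the booster injection".

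Table 11.1 assigns the SafAS to one row that covers both booster safety and safety follow-up, without saying whether the overall, per-dose or booster version is meant.

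Two further rules bear on the rates themselves. Section 11.1.1.2, which covers each separate vaccination including the booster, says: "In order to avoid any under-estimation of the incidences, the number of subjects with documented safety will be used as denominator of the frequencies". Section 8.3.4 says: "All vaccinated subjects with safety data, and all safety data recorded in the CRFs will be included in the safety analyses".

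The protocol foresees children who are primed but not boosted. Section 5.3.6.1: "The Investigator will discontinue the second or booster vaccination in the case of an event considered to be a definite contraindication". Section 5.3.6: "Withdrawn subjects will not be replaced".

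**The concern.** A population for describing what happens after the booster should consist of children who received it. As written, the closing sentence of Section 11.2.1.3 adds nothing to the overall safety set: each child's first study dose is a primary injection, so having had at least one dose and having had at least one primary injection describe the same children. Nothing in the sentence is specific to the booster.

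Safety in the 21 days after the booster is a stated objective (Section 2), and booster safety belongs to the final analysis (Section 11). If unboosted children count in the denominator but cannot contribute post-booster events, the rates are too low. Booster safety and booster immunogenicity would also describe different children. There is a presentational gap as well. Section 11.2.1.3 reports safety by the schedule received, and Section 5.1.1 allows the booster dosage to differ from the primary dosage, so a child without a booster may have no booster column to sit in.

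**Working it through.** **The plan's own figures.** The only numerical statement about safety is in Section 11.3: detection of an AE of 1% incidence with probability above 90% (N=240) and 70% (N=120). Using 1 − 0.99^n:

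- n = 240: 0.910
- n = 120: 0.701

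Both reproduce. Neither depends on how the booster set is defined.

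**The definitions side by side.**

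| Place | Must the child have had the booster? |
|---|---|
| 11.2.1.3, per-dose sentence, applied to the third dose | Yes |
| 11.2.1.3, booster sentence | No |
| 11.2.1.1, booster IAS | Yes |
| Table 11.1, booster safety row | Not stated (SafAS only) |

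The two sentences of Section 11.2.1.3 give different sets as soon as one primed child goes unboosted, and no text gives either precedence.

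**Does the denominator rule repair this?**

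- *Solicited reactions:* very probably yes. They come from the daily diary for days 0 to 7 (Section 8.3.3.2). The booster diary, DC3, comes after the injection and observation steps at the booster visit (Section 5.1.3, V07 or V08 depending on the design). A child who is not injected has no post-booster day 0 and no booster reactogenicity record, and so drops out under Section 11.1.1.2.
- *Unsolicited AEs and SAEs:* not assured. Section 11.1.1.2 does not say what makes safety documented for a particular dose. Section 8.3.4 admits vaccinated children with safety data, which literally includes a primed, unboosted child still in contact. Section 9.1.6 creates such a child: after a related seizure, vaccination ends but safety follow-up continues. Table 11.1 joins booster safety to follow-up in one row.

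**Size if the booster set were used literally as denominator.** Let d be the share of primed children not boosted.

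Reported rate = true rate × (1 − d)

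The protocol gives no value for d, so 5% to 20% is an assumption.

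| True rate | d = 5% | d = 10% | d = 20% |
|---|---|---|---|
| 10% | 9.5% | 9.0% | 8.0% |
| 30% | 28.5% | 27.0% | 24.0% |
| 50% | 47.5% | 45.0% | 40.0% |

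With whole children and 95% Clopper-Pearson intervals (the plan's method), for a true rate near 30%:

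- Pooled group of 120, d = 10%: 32/108 = 29.6% (21.2 to 39.2) becomes 32/120 = 26.7% (19.0 to 35.5).
- Pooled group of 120, d = 20%: 29/96 = 30.2% (21.3 to 40.4) becomes 29/120 = 24.2% (16.8 to 32.8).
- Cell of 30, d = 10%: 8/27 = 29.6% (13.8 to 50.2) becomes 8/30 = 26.7% (12.3 to 45.9).

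If the denominator rule removes every unboosted child, the denominators return to 108, 96 and 27, and the dilution is zero.

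**The case against.** A reader might infer that unboosted children necessarily enter the denominator and that all booster rates are therefore biased downwards. The documents do not support that. An analysis set is not a denominator. Section 11.1.1.2 sets the denominator separately, for the booster as for the other doses, and does so expressly to prevent under-estimation. For solicited reactions this answers the worry, and those are the events for which rates of 30% or 50% would be most natural.

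A correct set also exists already, since the booster is a dose and the per-dose sentence covers it. The closing sentence may have been meant for long-term follow-up, where a broader set is legitimate. Continued follow-up without further vaccination is spelled out only for a related seizure, with follow-up of discontinuations for related AEs in Section 5.3.6.4, so few children may be affected. The analyses are descriptive, no hypothesis is tested, and in a cell of 30 the shift is small beside the interval width.

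Nor should the change be defended on the ground that unboosted children are a selected group. A related SAE is a definite contraindication, so a boosted-only set is selected in the same way, and redefining the set does not remove that.

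These arguments limit the likely bias. They do not make the definition right: the sentence is labelled as the booster set, it conflicts with its neighbour, and the repair rests on a term left undefined per dose.

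**Conclusion.** The definition is wrong as written and should be corrected. The contradiction within Section 11.2.1.3 and the mismatch with the booster IAS are plain on the page and need no assumption.

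Dilution is possible, not certain. For solicited reactions it should be nil under Section 11.1.1.2. For unsolicited AEs and SAEs it lies between nil and a factor of (1 − d), that is 0.95 to 0.80 at an assumed 5% to 20% unboosted. On a true 30% the upper bound is a loss of 1.5 to 6 percentage points; on a true 10% it is 0.5 to 2 points. These bounds apply only if a follow-up contact counts as documented safety, or if the set is taken as the denominator in place of Section 11.1.1.2. The case for the change rests on the faulty definition rather than on the size of the bias.

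**What to change.** - In Section 11.2.1.3, replace the closing sentence with: *The SafAS for the booster vaccination is the subset of subjects who received the booster injection.*
- In Table 11.1, name that set for booster safety, and give safety follow-up its own entry.
- Keep the overall SafAS for SAEs over the whole study, and show SAEs in unboosted children separately so that none is lost.

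The cost is one sentence and one table row. No new data are needed and no clinical rule changes.
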